Subgroup analyses will give descriptive summaries of the primary and secondary outcomes (see Table 2) stratified by sex, race, education, and age (ages 65–72 and 73–80). Other subgroups may be defined based on baseline health variables (hip/waist ratio circumference, resting heart rate, blood pressure) and 30-day pre-intervention Garmin Vivofit 4 physical activity monitoring levels. These pre-specified subgroup analyses will be used to detect evidence for modification of the exercise treatment effect by each of the above covariates. These analyses will be done by testing the statistical significance of the interaction of each potential effect modifier with treatment. Conventional forest plots will be used, regardless of the outcome of statistical testing, to display point estimates and 95% confidence intervals for exercise effects of each potential effect modifier. These analyses will be reported as data-driven, exploratory, and hypothesis-generating.

Regression models will be developed in several domains to explore what factors may be associated with 18-month changes in the three primary outcomes: RAVLT_T1–5_, THV, and VO_2peak_. An example would include changes in blood-based anti-inflammatory, pro-inflammatory, neuronal, and AD-related biomarkers. For the IC group, primary outcome changes will be regressed with stationary bike performance over time: compliance, exercise duration, time in the target heart rate zone, and cadence. Given the limitations imposed by our sample size, these regression analyses will be considered exploratory but have the potential to provide valuable information regarding factors to consider in developing prediction models for future larger follow-up studies designed to more fully examine the neuroprotective mechanisms associated with high-intensity exercise in older elders at genetic risk for AD.

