### Participants

#### Inclusion criteria

The four primary inclusion criteria are: (1) APOE ε4 carrier (ε2/ε4, ε3/ε4, or ε4/ε4) determined initially by a saliva swab kit and confirmed with a blood test, (2) ages 65 to 80 inclusive, (3) no evidence of cognitive impairment based on neurocognitive screening tests (see below), and (4) an inactive physical activity level, defined as exercising less than 3 times per week at moderate-vigorous intensity. In addition, the potential participant must be fluent in English, a requirement for neuropsychological testing; have no plans to travel for more than 2 consecutive weeks during the 18-month intervention; and have in-home WIFI to connect to Peloton content and transmit exercise data.

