### Statistical analysis

#### Sample size and power

The CYCLE-AD RCT will compare changes from baseline to 18 months on the primary and secondary outcomes (see Table 2) in the UCC and IC randomized groups (75 per group). The sample size was estimated for each of the three primary outcomes: (1) trial 1–5 total recall on the RAVLT (RAVLT_*T1–5*_), (2) total hippocampal volume (THV), and (3) VO_2peak_. To determine the sample size necessary to detect a clinically meaningful difference between the groups for each primary outcome, we first estimated the variability (standard deviation) of the changes over 18 months in each variable from previous studies. Data for RAVLT_*T1–5*_ and THV are derived from our 18-month longitudinal study comparing high and low PA APOE ε4 carriers (Woodard et al., 2012; Smith et al., 2014); data for VO_2peak_ are derived from a published study (King et al., 1991). For each outcome, we calculated the pooled SD (combining intervention groups), and since the pooled SDs are only an estimate of the variability of changes that were observed from each study, we increased the pooled estimate to be equal to the upper 90th percentile of the SD distribution for each primary outcome. The assumed pooled and inflated SDs are: 17.15% for RAVLT_*T1–5*_, 4.35% for THV, and 3.16 ml/kg-min for VO_2peak_. Secondly, the size of the clinically meaningful difference to be detected between the groups for each outcome was determined based on the observed values seen in these previous studies. The differences to detect for changes over 18 months are: 9.5% for RAVLT_*T1–5*_, 2.4% for THV, and 1.75 ml/kg-min for VO_2peak_. These differences are similar to those actually observed in the cited studies and were selected to give similar sample sizes so that each aim would have adequate power with the same sample size. Hence, the detectable differences and SDs given above resulted in an estimated sample size for each primary outcome of 68 per group, assuming a power of 90% and a significance level of 5% (two-sided). Furthermore, we estimated that up to 10% of participants will not complete the 18-month measurements. Therefore, we inflated the sample size of 68 per group by 10%, yielding a study sample size target of 75 per group.

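### As naturally read, effect modification by age would be tested on two age bands; testing age as a continuous variable would use more of the information, and the text should say which is meant

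*Protocol article*

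**What the plan says.** All of this is in the protocol article, mainly under Data analysis.

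- The subgroup paragraph opens with description: "Subgroup analyses will give descriptive summaries of the primary and secondary outcomes", which are "stratified by sex, race, education, and age (ages 65–72 and 73–80").
- It then gives the same analyses an inferential purpose: "These pre-specified subgroup analyses will be used to detect evidence for modification of the exercise treatment effect by each of the above covariates". The method is "testing the statistical significance of the interaction of each potential effect modifier with treatment", with forest plots of estimates and 95% confidence intervals.
- Hip/waist ratio, resting heart rate, blood pressure and pre-intervention step counts are mentioned only as possibilities: "Other subgroups may be defined based on baseline health variables". No cut-points are given for them, and no bands are given for education.
- The status of the analyses is clear: "These analyses will be reported as data-driven, exploratory, and hypothesis-generating".
- The preceding paragraph names age as a possible ANCOVA covariate, without saying in what form.
- Inclusion criteria sets the age range, "2) ages 65 to 80 inclusive". No mean, SD or distribution of age is reported.

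**The concern.** Age is recorded as a number, but the only form the subgroup paragraph gives it is a two-way split. The sentence that introduces the interaction tests refers back to the subgroup analyses just described. An analyst following the text would therefore probably enter an indicator for age 73 or over into the interaction model. That treats a 72-year-old and a 73-year-old as different, and a 65-year-old and a 72-year-old as the same.

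The trial is sized for the main comparison of the groups, "assuming a power of 90% and a significance level of 5% (two-sided"), and not for interactions. An interaction test here starts with limited power. If the effect of exercise changes gradually with age, the split lowers that power further. What is at stake is the chance of noticing a real age gradient in an exploratory analysis.

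**Working it through.** **The plan's own figure.** Sample size and power states 68 per group for each primary outcome. With n = 2(1.960 + 1.282)² (SD/difference)²:

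- RAVLT: 21.01 × (17.15/9.5)² = 68.5
- Hippocampal volume: 21.01 × (4.35/2.4)² = 69.0
- VO2peak: 21.01 × (3.16/1.75)² = 68.5

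These agree with 68 to within rounding, and power at 68 per group is 89.6% to 89.8%. The figure concerns the main comparison. The article states no sample size or power for any interaction, so there is nothing further to reproduce.

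**Information kept by the split.** If the interaction is linear in age, the efficiency of the banded test relative to the continuous one is the squared correlation between age and the band indicator:

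retained = p(1 − p)(m₁ − m₀)² / Var(age),

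where p is the share aged 73 or over and m₁, m₀ are the mean ages in the two bands.

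With whole-year ages spread evenly over 65 to 80 (an assumption): p = 0.5, m₀ = 68.5, m₁ = 76.5, Var(age) = (16² − 1)/12 = 21.25. So retained = 0.25 × 8² / 21.25 = 16/21.25 = 0.753, a loss of about 25%.

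Other assumed age distributions, cut at 73:

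| Assumed ages | Share 73 or over | Retained |
|---|---|---|
| Even over 65–80, whole years | 50% | 75% |
| Truncated normal, centre 73, SD 4 | 50% | 68% |
| Truncated normal, centre 71, SD 4 | 33% | 65% |
| Truncated normal, centre 70, SD 4 | 25% | 61% |
| Truncated normal, centre 69, SD 4 | 19% | 56% |
| Truncated normal, centre 68, SD 4 | 14% | 51% |
| Truncated normal, centre 69, SD 3 | 10% | 40% |

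**What this does to power.** Take 136 completers (2 × 68), 1:1 allocation, two-sided 5%, and an interaction of b outcome SDs per SD of age. The noncentrality is b√136/2 for continuous age, multiplied by √retained for the bands. For b = 0.35 it is 0.35 × 11.66/2 = 2.04 with continuous age, and 2.04 × √0.753 = 1.77 with even bands.

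| b | Continuous age | Bands, even ages (0.753) | Bands, centre 70, SD 4 (0.61) |
|---|---|---|---|
| 0.20 | 21% | 17% | 15% |
| 0.35 | 53% | 43% | 36% |
| 0.50 | 83% | 72% | 62% |

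A simulation with 150 participants and 4,000 runs agreed in direction and rough size: power 0.775 continuous against 0.664 banded with even ages, and 0.776 against 0.573 with normal ages.

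**How large these interactions are.** The designed main effect is about 9.5/17.15 = 0.55 SD. With b = 0.35, the effect would be 0.55 − 0.35 = 0.20 SD at one SD of age on one side of the mean and 0.55 + 0.35 = 0.90 SD on the other. That is a strong gradient. At b = 0.20 the test is weak in either form.

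**The case against.** The strongest reply is that the article never says the interaction test uses banded age. The bands sit in the sentence on descriptive summaries, and the test sentences give no functional form. How a covariate is coded in an exploratory model is commonly left to an analysis plan, which is not shown. This stands in part: a reader might infer that the protocol fixes a dichotomised test, and the text does not go that far. But the sentence on detecting effect modification points back to the subgroup analyses as described, and the bands are the only form of age in that description. The wording steers an analyst towards the split, so the point is not merely about a missing detail.

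A second reply is that no fixed percentage loss can be claimed. That stands. A reader might take a figure such as 25% to 36% as a property of this trial. It is not, because the article reports no age distribution. Several younger-skewed shapes lose more, up to about 60% in the cases above. If the true effect is a step at the cut, banding loses nothing.

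Third, one might extend the criticism to blood pressure, resting heart rate, hip/waist ratio and step counts. The document does not support that, because it says only that such subgroups may be defined and gives no cut-points.

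Finally, bands have some merit: they need no linearity assumption and they match the forest-plot rows. That is a good reason to keep them for display. It does not make them the better basis for the test when the effect changes gradually.

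**Conclusion.** The point holds as a minor improvement. As naturally read, the age interaction would be tested on the 65–72 against 73–80 split, though a continuous test is not ruled out. If the interaction is roughly linear, the split keeps about 75% of the information with ages even over 65 to 80, and less if enrolment is skewed young. In the illustrative cases that costs about 10 percentage points of power or more at b = 0.35 and 0.50, but only about 4 to 6 points at b = 0.20.

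These sizes rest on assumed age distributions, a linear interaction and 136 completers. Only the last of these follows from the plan's own numbers. The analyses are labelled exploratory, and the primary comparison and the sample size are unaffected.

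**What to change.** State in the analysis text that the treatment-by-age interaction is tested with age as a continuous variable, and that the two bands are kept for descriptive tables and forest-plot rows. Apply the same principle to any other continuous baseline variable that is actually used as a modifier.

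The cost is one line of wording and no new data. The downside is an assumed linear interaction, which the banded estimates let readers check by eye. If the sponsor already intends a continuous test, the same line removes the ambiguity. It should be settled before the unblinded group comparison that the Introduction places shortly after follow-up ends in mid-2026.

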## Discussion

The CYCLE AD RCT was designed to parallel our 18-month longitudinal observational studies (Smith et al., 2011; Woodard et al., 2012; Smith et al., 2014; Smith et al., 2016) comparing low-exercise (< 3 times per week) versus high-exercise (≥ 3 times per week) ε4 carriers. The neuroprotective properties of exercise that we observed in brain atrophy and cognition may have resulted from lifelong habitual levels of exercise. A recent epidemiological study, however, noted that low-exercise individuals who become fit by increasing their exercise levels reduced their chances of developing dementia, similar to those who were fit for most of their lives (Tari et al., 2019). The CYCLE-AD trial, therefore, will test the concept that a high-intensity aerobic exercise intervention initiated later in life can maintain CNS function and offer neuroprotection.

A unique feature of the CYCLE-AD trial is the long duration of the exercise intervention (18 months). In a 2019 meta-analysis (Falck et al., 2019), Falck et al. reviewed 56 exercise intervention studies and noted that the median intervention duration was a relatively brief 4.6 months (75th percentile < 9.5 months). Meta-analyses suggest that longer exercise program durations in clinical trials are associated with greater gains in fitness (VO2max) (Silva et al., 2014; Borde et al., 2015; Oja et al., 2018) and maintenance of cognition (Colcombe and Kramer, 2003) in older adults, which could, in turn, offer greater neuroprotection for individuals at genetic risk for AD.

Another unique aspect of CYCLE-AD is the utilization of a consumer home-based exercise platform (Peloton Indoor Cycle), which offers many potential benefits to facilitate long-term exercise (Costello et al., 2011; Collado-Mateo et al., 2021). Sedentary older adults report feeling intimidated by fitness facilities and express concerns about keeping up with others in a group exercise setting (Costello et al., 2011); thus, a home-based intervention may serve as a facilitator for exercise in this cohort. Time is also frequently reported as a key barrier to initiating and maintaining consistent exercise (Costello et al., 2011); on-demand 24-h streaming exercise classes are predicted to enhance participant adherence by not requiring the participant to spend time traveling to a laboratory or exercise facility and follow a rigid class schedule. Supervision has been identified as another key aspect of exercise facilitation because it increases accountability, adherence, and quality of exercise performance (Collado-Mateo et al., 2021); the CYCLE AD exercise intervention, while delivered remotely, maintains a high level of oversight by using objective and frequent data monitoring. The exercise physiologist has remote access to the frequency, intensity, and duration of exercise and specific exercise performance variables (e.g., heart rate, cadence, power) from each exercise session on the Peloton portal. The use of objective exercise performance data removes the need for participant self-reported exercise adherence, which is well-documented to be highly variable and inaccurate (Prince et al., 2008; Hukkanen et al., 2018; Fiedler et al., 2021). Thus, this model of monitoring facilitates a shared decision-making approach between the exercise physiologist and participant, which is predicted to increase adherence to the study protocol and reduce potential study withdrawals.

Compared to continuous exercise training (CET; e.g., walking or running on a fixed incline treadmill at a fixed speed), virtually all Peloton classes, ranging from easy to difficult, involve high-intensity interval training (HIIT) in which the cycling instructors frequently ask the participants to vary the cadence, resistance, or both, enabling rapid fluctuations between low and moderate intensities or between moderate and high intensities. HIIT has three major advantages relative to CET: (1) HIIT is more efficient at improving fitness given the same exercise duration compared to CET (Gibala and McGee, 2008). (2) Frequent modulations of exercise intensity, as is accomplished with HIIT, reduce participant boredom, especially when instructions are delivered through an engaging and convenient streaming platform. (3) HIIT results in significantly greater improvements in memory functioning than CET in low-exercise healthy elders (Kovacevic et al., 2019). Thus, the capability to leverage the advantages of both HIIT and CET is anticipated to keep participants engaged and exercising at relatively high-intensity levels throughout the trial.

CYCLE-AD will test the efficacy of high-intensity aerobic exercise using an indoor cycle rather than a treadmill. Older adults prefer cycling to running (Reitlo et al., 2018) because the former does not involve whole-body load bearing, a key factor for elders with orthopedic injuries, arthritis, or chronic pain. In addition, unlike a treadmill, intensity transitions associated with HIIT can be accomplished quickly and efficiently on a cycle by varying cadence, resistance, or both. In contrast, treadmills are not quick and efficient in switching speed and incline angle.

Demonstrating positive results in the CYCLE-AD RCT will have a substantial impact on the field of AD. For older adults, the validation of an exercise program that could be initiated after decades of inactivity would empower them to take an active role in the prevention of AD. From a public health perspective, the identification of an exercise intervention that could contribute to delaying dementia onset by 5 years is estimated to reduce the prevalence of Alzheimer’s Disease and Related Diseases (ADRD) by 37%; delaying dementia by just 2 years reduces prevalence by 16% (Vickland et al., 2010). Our previously published data (Smith et al., 2011; Woodard et al., 2012; Smith et al., 2014; Smith et al., 2016) indicate that AD-related disease progression, as measured by memory testing and hippocampal volume, can be slowed in genetically high-risk individuals who exercise regularly. If successful, the CYCLE-AD trial has the potential to provide a scalable, low-cost intervention capable of substantially reducing healthcare costs by altering the disease trajectory of ADRD.
